### Safety analysis: adverse events and serious adverse events

Subjects were monitored for all adverse events (AE) immediately following bronchoscopy until deemed medically stable and ready for discharge and again at 30 days after study enrollment by way of a phone call with the subject. Subjects were monitored for serious adverse events (SAE) for two years following enrollment.

Possible AEs included, but were not limited to, fatigue, muscle aches, bitter taste in mouth, dry or sore throat, hoarseness, fever [greater than 100 °F for more than 24 hours], bronchospasm, arrhythmia, pneumothorax, hemoptysis, shortness of breath and infections. A SAE was defined as any serious effect on the health or safety or any life-threatening problem or death caused by, or associated with the study procedure if that effect, problem or death was not previously identified in the investigational plan or application. These included hospitalization [≥24 hours], death, disability, or any event that require intervention to prevent damage.

AEs and SAEs were documented and classified in terms of severity [mild, moderate, severe], expectedness [expected or unexpected] and relatedness [unlikely, possibly, probably or unknown]. A medical monitor at the data coordinating center ([name] at Henry Ford Health System) worked closely with each site PI and ultimately was responsible for the final determination of SAE relatedness. Treatments or interventions and outcomes also were documented.

### Statistical analysis

Statistical significance was determined using an F-test of equality of variances following by a Student’s t-test for comparison of groups on continuous variables and Chi square or Fisher exact test for categorical variables. Differences were considered significant if *p* < 0.05. Power analysis was conducted as described above in the Revised Study Design section.

## Results

Here we present the baseline characteristics of the enrolled LCRT cohort, and results for secondary endpoints that have been reached including safety analysis and establishment of the NBEC and peripheral blood sample biospecimen repository.

### Enrollment

Accrual for the LCRT study was completed in March 2012. We enrolled 403 subjects with demographic risk factors for lung cancer into a prospective multi-site, blinded LCRT study, performed bronchoscopy at enrollment, and collected NBEC and blood (buffy coat and plasma) samples from each subject (Fig. 1). Of the 403 subjects enrolled, 288 were enrolled at the time of a standard of care (SOC) bronchoscopy done for diagnostic purposes and 115 were enrolled at time of a volunteer study driven (SD) bronchoscopy. Of the 288 SOC bronchoscopies, 64 were done to evaluate for lung cancer, 34 for monitoring following lung transplantation, and the remaining 190 for a variety of indications. Of the 403 subjects enrolled, 18 were removed from the study as screen failures due to diagnosis of prevalent lung cancer at enrolling bronchoscopy or subsequent tests and one subject withdrew from the study leaving 384 subjects in the cohort. We conducted a descriptive analysis of baseline data for the 384 remaining subjects.

**Fig. 1 Fig1:**
[figure not shown]
Summary of Enrolled Cohort

### Demographic information

Subject population characteristics are shown in Table 1. Of the 384 subjects, mean age was 62.9 ± 8.2 years with a mean smoking history of 50.4 pack years. Thirty-four percent were current smokers and approximately 10 % were concomitant cigar and/or pipe smokers. The cohort included 213 males (55 %) and 171 females (45 %), 89 % Caucasians, 10 % African Americans, and 1 % other. Sixty percent of subjects were married or living with a partner, 30 % were widowed, and 10 % were single. A majority (66 %) were high school graduates with or without some college less than a bachelor’s degree, 10 % held a bachelor’s degree and 6 % held an advanced degree. Reported income was less than $40,000 per year pt?>in 37 % of subjects although 31 % of subjects (120 individuals) chose not to provide household income information. Forty-six percent were retired and 17 % were disabled (Table 1). Work-related exposures were reported by 234 (61 %) of subjects with the highest percentages being asbestos (*n* = 54, 14 %), farming (*n* = 41, 11 %), chemicals or plastics (10 %), welding (10 %), foundry or steel milling (9 %), and painting (9 %) (Additional file 2: Table S2). Each subject had a chest CT scan at the time of enrollment; 242 subjects (63 %) had a clinically indicated (standard of care) CT scan within three months prior to enrollment and the remaining 142 (37 %) had a research driven CT scan within 2 weeks of enrollment. Twelve percent of subjects were undergoing evaluation for lung cancer at time of enrollment and were negative for cancer (Additional file 3: Table S3). Based on responses to baseline questionnaire, self-reported prevalence of chronic obstructive pulmonary disease (COPD) was 41 % (*n* = 156), chronic bronchitis 18 % (*n* = 68), and emphysema 28 % (*n* = 106) (Additional file 3: Table S3). Because Pulmonary Function Test (PFT) data were available for most subjects, it was possible to compare self-reported COPD prevalence to test data (see below). Prevalence of other self-reported lung diseases were: interstitial lung disease 9 % (*n* = 35), and sarcoidosis 3 % (*n* = 10) (Additional file 3: Table S3).

**Table 1 Tab1:** LCRT Subject Characteristics

Baseline characteristics	*n* = 384
Age in years [mean (SD^a^)]	62.9 (8.2)
Age in years [median]	62
Male	213 (55 %)
Female	171 (45 %)
Caucasian	343 (89 %)
African American	37 (10 %)
Other or not reported	4 (1 %)
Cigarette pack years [mean (SD)]	50.4 (25.5)
Cigarette pack years [median]	43
Age in years at smoking inception [mean (SD)]	16.1, 3.8
Age in years at smoking inception [median]	16
Total years of smoking [mean (SD)]	37.4 (10)
Total years of smoking [median]	38
History of cigar use	35 (9 %)
History of pipe use	29 (8 %)
Married or living as married	231 (60 %)
Widowed	116 (30 %)
Single	37 (10 %)
Less than high school education	52 (14 %)
High school diploma or GED^b^	118 (31 %)
Associate degree or some college	136 (35 %)
Bachelor's degree	40 (10 %)
Graduate degree	24 (6 %)
Other or not reported	14 (4 %)
Employed	109 (28 %)
Unemployed	30 (8 %)
Retired	175 (46 %)
Disabled	64 (17 %)
Other or not reported	6 (2 %)
Income < $40,000/year	141 (37 %)
Income > $40,000/year	123 (32 %)
Other or not reported	120 (31 %)

^a^SD = standard deviation

^b^GED = Graduate Educational Development

### SOC vs SD bronchoscopy characteristics

The intended population for the LCRT includes both subjects for whom diagnostic bronchoscopy is indicated who also will benefit from LCRT measurement and subjects who will have bronchoscopy only to obtain NBEC samples for LCRT measurement. Therefore, we compared baseline characteristics between the SOC and SD bronchoscopy subject groups, which represent each of these respective intended population categories. Of 384 subjects enrolled, bronchoscopy was SOC in 269 (70 %) and SD in 115 (30 %). There were no significant differences in in pack years smoked (Additional file 4: Table S4). SD subjects were slightly younger (mean age of 61.5 compared to 63.6, *p* = 0.021), more likely to be current smokers (55 % vs. 25 %, *p* < 0.001), and less likely to have COPD (41 % vs. 60 %, *p* = 0.002) (Additional file 4: Table S4).

### Lung cancer screening eligible sub-group

The USPSTF age and smoking pack year eligibility criteria for lung cancer screening by annual low-dose helical chest CT are 55–80 years and a minimum of 30 pack-years, respectively. Among subjects enrolled into the LCRT study, 253/384 (65.9 %) were eligible for annual screening at enrollment, according to these criteria. Seventy subjects did not meet the minimum age criterion at time of enrollment. By the 2016 follow up time point, 45 of these 70 will be eligible for screening and 69/70 will be eligible by the 2018 follow up.

### Chronic obstructive pulmonary disease

We assessed COPD status in the enrolled cohort because COPD is an independent risk factor for lung cancer [30–38]. COPD was defined using GOLD criteria based on pulmonary function test (PFT) data [39]. Demographic information relative to COPD status is displayed in Table 2. PFT information was available for 290 subjects. Fifty-four percent of these (157 subjects) had COPD based on PFT. Among the 157 subjects with COPD based on PFT, COPD severity was GOLD stage 2 or worse in more than 70 % based on established criteria [39]. Mean FEV1/FVC was 0.52 for the 157 subjects with COPD (all stages) compared to 0.78 for the 133 without COPD. Those with COPD were more likely to be male (62 % vs. 38 % female, *p* = 0.027) and have a higher mean pack year smoking history (56 vs. 45 for non-COPD, *p* < 0.001). No differences were noted in age, race or smoking status (current vs. former smokers) (Table 2.)

**Table 2 Tab2:** Chronic Obstructive Pulmonary Disease by PFT

Classification	n	M/F^a^	Mean age	Race	Smoking status	Pack years	FEV1%^d^	FEV1/FVC^e^
			in years	C/AA/Other^b^	current/former	smoked^c^		
No COPD	133	65 / 68	62	113 / 16 / 4	46 / 87	45	80	0.78
COPD (all)	157	97 / 60	63	145 / 12 / 0	50 / 107	56	58	0.52
COPD (stage 1)	45	32 / 12	62	41 / 4 / 0	22 / 23	54	76	0.59
COPD (stage 2)	77	48 / 29	64	73 / 4 / 0	22 / 55	57	57	0.55
COPD (stage 3)	26	15 / 11	64	23 / 3 / 0	5 / 21	53	35	0.39
COPD (stage 4)	7	2 / 5	63	7 / 0 / 0	1 / 6	65	22	0.27
COPD (stage unknown)	2	1 / 1	66	1 / 1 / 0	0 / 2	66	-	0.57
Unknown	94	50 / 44	63	85 / 9 / 0	35 / 6 0	50	-	-

^a^M = male, F = female

^b^C = Caucasian, AA = African-American, Other = other race or race not reported

^c^Pack years = packs of cigarettes smoked per day x years of smoking

^d^FEV1% = forced expiratory volume in 1 second, percent of expected

^e^FEV1/FVC = FEV1/Forced Vital Capacity

Of the 157 subjects with COPD based on PFT criteria, clinical history of COPD based on self-report or chart review was available for 150. Overall, self-reported status matched the diagnosis by PFT in 67 % (Additional file 5: Table S5.).

### Lung transplant

Nine percent (34 subjects) of our cohort had received a (single) lung transplant prior to enrollment. We evaluated differences between lung transplant and non-lung transplant subjects to determine if there were comparable demographic risk factors for lung cancer. Age (62.9 vs. 63.9 years, *p* = 0.202), gender, race and smoking history (51.7 vs. 50.0 pack years, *p* = 0.681) were statistically similar, but 100 % of transplant subjects were former smokers compared to only 63 % of non-transplant subjects (*p* < 0.001). Prevalence of COPD was comparable, 62 % vs. 53 %, *p* = 0.648. Interstitial lung disease, however, was more prevalent among transplant subjects 29 % vs. 7 %, *p* < 0.001 (Additional file 6: Table S6).

### Establishment of NBEC and peripheral blood sample biospecimen repository

Matched blood and NBEC were collected for 361/384 (94 %) subjects and banked in multiple aliquots. Blood samples were processed at each site at the time of collection to generate 2 aliquots of buffy coat and 2–5 aliquots of plasma from each subject. These aliquots were frozen and stored at −80 °C until shipment to the Early Detection Research Network (EDRN) Biorepository in Fredrick, MD. One aliquot of buffy coat was transferred to the University of Toledo for analysis and the other remains in storage. NBEC were stabilized at each site in RNA Later (Ambion, Austin, TX) and shipped along with matching slides to ResearchDx, Irvine, CA. RNA was extracted from NBEC within 24–48 hours of receipt, assessed for quality and quantity and stored in aliquots at −80 °C. One NBEC RNA aliquot was shipped to the University of Toledo for analysis for those samples with a minimum yield of 1 microgram and aliquots for each subject remain in storage at ResearchDx.

At the University of Toledo, genomic DNA (gDNA) was extracted from one aliquot of buffy coat derived from the blood sample from approximately 80 % of subjects and 100 % of these yielded gDNA of sufficient quality and quantity for proposed molecular studies. The quality and quantity of NBEC RNA from approximately 40 % of subjects has been assessed to date. RNA from each sample was treated with DNase I, tested via PCR to ensure removal of contaminating gDNA from the RNA and then reverse transcribed into cDNA. For 90 % of subjects the cDNA generated from these purified NBEC RNA samples was PCR amplifiable and of sufficient quantity to perform LCRT testing. Additional aliquots of RNA remain for the roughly 10 % of samples that did not pass this quality control. Samples from over 120 subjects were used successfully in preliminary targeted next generation sequencing (NGS) RNA sequencing analysis studies.

### Lung cancer incidence

Two years following initiation of the study, 5 subjects (1.3 %) without prevalent lung cancer developed bronchogenic carcinoma. Due to the blinded status of the LCRT study, no further details are available regarding these subjects.

## Discussion

### Enrolled cohort is representative of LCRT target population

The target population of the LCRT biomarker is individuals who meet USPSTF eligibility criteria for annual low dose helical CT screening [2]. The enrollment criteria for the LCRT study included both current and former smokers, individuals with and without concurrent pulmonary disease and/or respiratory exposures as well as both subjects undergoing medically recommended bronchoscopy (SOC group) and volunteers (SD group). At the time of enrollment into the LCRT study, most subjects (66 %) met USPSTF age and smoking pack-year eligibility criteria (55–80 years of age, ≥ 30 pack years). Additionally, most of those not eligible at enrollment will be eligible for screening by the 2016 follow up time point due to increased age, and this fraction is expected to further increase at the 2018 follow up. Therefore, this group is highly representative of the LCRT biomarker target population.

### Feasibility to reach LCRT study endpoint based on cohort characteristics

Based on demographic characteristics of the enrolled population (Table 1), we expect lung cancer incidence in the LCRT study to be similar to the 3.1 % incidence over 3.9 years reported by Bach et al. [40] in which mean age was 60.1 and smoking history of 52 pack-years. The five incidental lung cancers observed two years after initiation of the study are consistent with this rate. Taking into account that some of the 384 study subjects will have died from causes other than bronchogenic carcinoma prior to these time points and that some will be lost to follow up we estimated incidental lung cancers in the cohort based on 300 subjects. As such we expect to observe approximately 12 incidental lung cancers by the 2016 follow up (mean time since enrollment approximately 5 years) and 17 by the 2018 follow up point (mean time since enrollment approximately 7 years), which will be more than sufficient to reach the proposed endpoint of a risk ratio of ≥ 5.0.

### Feasibility of LCRT implementation (safety and acceptance by subjects)

The LCRT biomarker requires a one-time acquisition of NBEC through bronchial brush biopsy at the time of bronchoscopy. In addition to the LCRT study, Department of Defense Lung Cancer Research Program, and NIH recently funded other large studies assessing utility of biomarkers measured in NBEC obtained at bronchoscopy intended to more accurately determine lung cancer risk and/or to enable early lung cancer diagnosis ([name], Clinicaltrials.gov NCT01475500 CA152662 and CA102353; [name], Clinicaltrials.gov NCT02504697 DECAMP-2 and CA164783-04; [name], CA152751-05S2). Therefore, it is important to carefully evaluate the safety and comfort of this procedure, which will impact general acceptance by patients and clinicians. Based on published studies, bronchoscopy with or without biopsy is considered a safe procedure and it is used not only for medical purposes but also to conduct research [5, 41–49]. Reported complication rates (also known as serious adverse event/SAE rates) for all bronchoscopy procedures range from 0.08-1.93 % and mortality rates range from 0.004-0.045 % [50–52]. One large Japanese study of almost 50,000 patients who underwent bronchoscopy with brush biopsy in either central or peripheral airways reported a complication (SAE) rate of 0.46 %. This risk of complication is similar to the 0.28-0.32 % complication (SAE) rate reported for colonoscopy [53, 54] which is routinely used and repeated for colorectal cancer screening. Importantly, a bronchoscopy with brush biopsy limited to the *central airways* for collection of NBEC, the procedure used here, virtually eliminates risk for the primary complications reported to be associated with bronchoscopy, including pneumothorax or significant hemorrhage. Consistent with this, we observed no SAE associated with bronchoscopic brush biopsy in the subjects enrolled based on SD bronchoscopy.

It is particularly important to assess safety and comfort in the subjects meeting accepted criteria for lung cancer screening, a group that has increased prevalence for numerous comorbidities. Results from at least one previous report have suggested that research bronchoscopy and brush biopsy can be safely performed in subjects with heavy smoking history and those with obstructive lung disease [45]. Previous guidelines have suggested that an FEV1 less than 60 % is considered a contraindication to performing research driven bronchoscopy. However, bronchoscopy in adults with stable asthma and COPD has been performed safely at lower values of FEV1 [55]. Pulmonary function test data were available for more than 75 % of the subjects enrolled here (290 of 384 subjects). One hundred fifty-seven had clinical COPD and more than 70 % had GOLD stage 2 or worse (Table 2). Additionally, 9 % of enrolled subjects had a history of interstitial lung disease, 9 % were single-lung transplant recipients and a small percentage had other pulmonary disease (Additional file 3: Table S3) and bronchoscopy was safely performed on all of them. Specifically, no complications (SAEs) were associated with bronchoscopic brushing and sample collection in either standard of care (SOC) or study driven (SD) group.

In summary, bronchoscopic brush of the central airways to collect NBEC for lung cancer risk analysis was safe and well-tolerated in this study of subjects demographically at risk for lung cancer, including those with significant co-morbid conditions. Because the AE rate was much lower than that reported for routinely used screening colonoscopy [53] we expect that this procedure will be acceptable to patients and clinicians if the LCRT or other tests in development are validated to identify subjects with increased risk for lung cancer and/or early stage lung cancer.

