## Methods

### Study design

This LCRT study (Clinicaltrials.gov, NCT 01130285) was conducted after approval by an institutional review board at each participating institution (University of Toledo Medical Center, Mayo Clinic, University of Michigan, The Toledo Hospital, Ohio State University, Vanderbilt University Medical Center/Tennessee Valley VA Medical Center, Henry Ford Health System, National Jewish Health, Medical University of South Carolina, Inova Fairfax Hospital, Cleveland Clinic Foundation and Mercy St. Vincent Medical Center, see Additional file 1: Table S1) and under a Federal Drug Administration (FDA) approved Investigational Device Exemption (IDE G090273). The original design to assess the clinical utility of the LCRT biomarker was a prospective, blinded, nested case–control study. The original primary endpoint was prediction of risk for development of lung cancer with an odds ratio of at least 5.0. It was estimated that there would have been sufficient power to test this endpoint by enrolling approximately 800 subjects and following them for 3 years, resulting in identification of at least 15 prospective lung cancer cases. LCRT analysis would then be conducted in NBEC of the 15 cases and 120 matched controls. However, the study was revised to a prospective cohort design due to a) advances in technology that enable cost-effective measurement of LCRT in all subjects, and b) the greater power associated with this design. The new design and primary endpoints are described below.

The secondary endpoints and analyses are unchanged and include: 1) determination of study safety at day 30, 2) establishment and maintenance of a biospecimen repository of biological specimens derived from NBEC [RNA and cytology slides] and corresponding blood samples [peripheral blood leukocyte Buffy Coat and frozen plasma] from the subjects enrolled, 3) analysis of the predictive ability of LCRT positive for lung cancer including sensitivity, specificity, positive predictive value, and negative predictive value, 4) calculation of absolute risk of LCRT positive for lung cancer and, 5) measurement of the incidence of lung cancer in the study cohort every two years until the end of study. Additionally, we will explore the influence of demographic or clinical variables for lung cancer on the predictive ability of LCRT.

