### Enrollment

Subjects were considered enrolled in the LCRT study when they underwent the study procedure (bronchial brush biopsy with NBEC sample collection). All enrolled subjects had a CT of the chest performed within 3 months prior to study entry or a research driven CT scan within two weeks after study entry to rule out prevalent lung cancer. Study eligibility, including smoking history, was assessed through initial contact interview by a trained clinical coordinator at each site. The initial Contact Report Form (CRF) was designed to allow for computation of number of pack-years of cigarettes smoked as well as a detailed smoking history that included information on periods of smoking cessation and use of other forms of tobacco such as pipes and cigars. The CRF also contained questions on personal history of selected diseases, stroke, and diabetes, family history of lung cancer, occupational history (jobs and industries either previously demonstrated or thought to be associated with increased risk for lung disease or lung cancer), education, and marital status.

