### Sample collection

Standardized sample collection kits were provided to each site. Kits contained supplies for the collection and labeling of biological samples including a disposable bronchial cytology brush (ConMed Corporation, Utica, NY ref.#149) for the collection of NBEC, a 10 ml K_2_-EDTA vacutainer tube (Becton, Dickinson and Company, Franklin Lakes, NJ ref.#366643) for the collection of whole blood and barcoded stickers. Following positioning of the bronchoscope, the cytology brush was inserted and NBEC were collected from a grossly normal region of either main stem bronchus. For SOC bronchoscopies, this occurred immediately after the diagnostic procedures on the opposite side or in a separate area from the lung region under clinical investigation. If the patient had received a lung transplant, the specimen was obtained from the recipient native mainstem bronchus. The brush was withdrawn, shaken into a tube of normal saline chilled on ice and re-inserted into the bronchoscope for collection of additional NBEC. This procedure was repeated a total of 5–10 times. After the last brushing, the cytology brush was shaken in the saline and then dabbed onto a glass slide to enable assessment by a pathologist. Immediately prior to or immediately following bronchoscopy, approximately 10 ml of whole blood was obtained using standard phlebotomy techniques into a K_2_-EDTA vacutainer tube. Blood and NBEC samples were transferred to the lab within 10 min. for processing and stabilization, which was initiated within 1 hour post-collection.

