## Conclusions

The demographic composition of the enrolled group is representative of the population for which the LCRT is intended. Specifically, based on baseline population characteristics we expect lung cancer incidence in this cohort to be representative of the population eligible for LDCT lung cancer screening. Collection of NBEC by bronchial brush biopsy/bronchoscopy was safe and well-tolerated in this population. These findings support the feasibility of testing LCRT clinical utility in this prospective study. If validated, the LCRT has the potential to significantly narrow the population of individuals requiring annual low-dose helical CT screening for early detection of lung cancer and to enable safe delay the onset of screening for individuals with results indicating low lung cancer risk. For these individuals, the small risk incurred by undergoing once in a lifetime bronchoscopic sample collection for LCRT may be offset by a reduction in their CT-related risks. The LCRT biospecimen repository will enable additional studies of genetic basis for COPD and/or lung cancer risk.

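### Serious adverse events are defined and summarised by their link to the brushing, but the safety conclusion extends to bronchoscopy done only for the LCRT, for which the 115 study-driven subjects are the direct evidence

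*Protocol article*

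**What the plan says.** The Study design section lists "determination of study safety at day 30" among the secondary endpoints. The Enrollment section counts subjects as enrolled "when they underwent the study procedure (bronchial brush biopsy with NBEC sample collection". The parenthesis describes the study procedure as brushing and collection and does not name the bronchoscopy that carries the brush.

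The Safety analysis section has two layers. Adverse events of every kind were watched for from the end of bronchoscopy until discharge, and again by phone at 30 days. Each event was graded for severity, expectedness and "relatedness [unlikely, possibly, probably or unknown". A serious adverse event, however, is one that the study procedure caused or with which it was associated. The Follow up section ties the 30-day contact to events possibly related to that same procedure.

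On the order of work within a session, the Sample collection section says: "For SOC bronchoscopies, this occurred immediately after the diagnostic procedures on the opposite side or in a separate area".

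The visible safety summaries are worded around brushing. The Abstract reports no severe events associated with it. The Discussion says the same of serious events in the study-driven (SD) group, and then for both groups: "no complications (SAEs) were associated with bronchoscopic brushing and sample collection in either standard of care (SOC) or study driven (SD) group". The Conclusions go wider: "Collection of NBEC by bronchial brush biopsy/bronchoscopy was safe and well-tolerated in this population". They also set the risk of a one-off bronchoscopic collection against a lower CT-related risk. The section comparing standard-of-care (SOC) and SD subjects names two kinds of intended user: people who need a diagnostic bronchoscopy anyway, and "subjects who will have bronchoscopy only to obtain NBEC samples for LCRT measurement".

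**The concern.** The count and the conclusion concern different exposures. The count is of serious events tied to brushing. The conclusion is about bronchoscopy, including bronchoscopy that would not take place without the test. For a test-only user, every part of the procedure is a cost of the test, so an event belongs in the count whether or not the brush caused it.

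The difference matters most in the SOC group. There the diagnostic work came first in the same session, so an event judged to arise from it is correctly not attributed to brushing. A zero count in that group therefore says that brushing adds little to a bronchoscopy already under way. It does not say what a bronchoscopy costs someone who had no other reason for one.

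At stake is the benefit-risk sentence in the Abstract and Conclusions. The lung cancer primary endpoint is not affected.

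**Working it through.** **Group sizes (Enrollment results; SOC vs SD section).** 288 SOC + 115 SD = 403 enrolled. 403 − 18 screen failures − 1 withdrawal = 384. 384 − 115 = 269 SOC, and 288 − 269 = 19, so all removals came from the SOC group and the SD denominator is 115 either way. Shares: 269/384 = 70.1 %; 115/384 = 29.9 %. These agree with the article's 70 % and 30 %.

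**What each group can show.**
- SOC, 269 subjects: bronchoscopy was clinically indicated and brushing was added after the diagnostic work. A brushing-attributed count estimates the added risk of brushing, which is the relevant quantity for the first kind of intended user.
- SD, 115 subjects: bronchoscopy was done for research. A count over the whole procedure estimates the risk for the second kind of user. These subjects had a mean age of 61.5 versus 63.6 years (p = 0.021) and COPD in 41 % versus 60 % (p = 0.002), so carrying their result over to users with more lung disease needs care.

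**The stated figure.** The article gives zero brushing-associated serious events in each group. This cannot be reproduced without event listings, and the whole-procedure count in SD subjects is not in the text at hand. The best case is taken below as an assumption: zero whole-procedure events in 115.

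**Exact limit for zero events in n subjects.** The two-sided 95 % upper limit solves (1 − p)^n = 0.025, so p = 1 − 0.025^(1/n). The one-sided 95 % limit uses 0.05 in place of 0.025.

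| n | two-sided 95 % upper limit | one-sided 95 % upper limit |
|---|---|---|
| 115 (SD) | 3.16 % | 2.57 % |
| 269 (SOC) | 1.36 % | 1.11 % |
| 384 (both) | 0.96 % | 0.78 % |

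**Against the article's own yardsticks.** The Discussion cites a 0.46 % complication rate for bronchoscopy with brush biopsy, and 0.08 % to 1.93 % across bronchoscopy procedures. These are rates for the whole procedure.
- At 0.46 %: expected events in 115 are 115 × 0.0046 = 0.53, and the chance of none is (1 − 0.0046)^115 = 0.59.
- At 1.93 %: expected events are 115 × 0.0193 = 2.22, and the chance of none is (1 − 0.0193)^115 = 0.11.

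Zero events in 115 would therefore be the more likely outcome at the cited 0.46 %, and would not be remarkable even at the top of the range.

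**The case against.** The strongest reply is that safety was not confined to brushing. The endpoint is study safety at day 30, and all adverse events after bronchoscopy were monitored and graded. This stands. A reader might infer that only brushing events were captured, but the documents do not support that. The restriction lies in the definition of a serious event and in the wording of the summaries.

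Second, for SD subjects the study procedure may have been meant to include the bronchoscopy: the Discussion describes bronchoscopy with central-airway brushing as the procedure used. This is possible, but the Enrollment parenthesis reads otherwise and the article does not settle it.

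Third, brushing attribution is right for SOC users, who are also an intended population. Counting every event in SOC sessions could overstate the risk for a test-only user. This stands, and it is why the two groups need separate tables.

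Fourth, the article already makes a separate statement for SD subjects, and no visible text gives a pooled safety rate over 384 or 403. A charge that the larger number is presented as the evidence has no sentence behind it.

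Fifth, part of the article was not available for this review and may hold safety results. It would be wrong to infer that bronchoscopy-related events went unreported, or that risk has been shown to be understated. Nor is the absence of a counting rule for unknown relatedness a finding, since an article may leave that to the full protocol.

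**Conclusion.** The point holds in a limited form. The definition of a serious event and the visible summaries are tied to brushing, while the conclusions and the benefit-risk statement reach bronchoscopy done only for the test. For that use the direct evidence is 115 of 384 subjects (30 %). Even if their whole-procedure count is zero, the data are compatible with a rate of up to about 3.2 % (two-sided 95 %). The other 269 (70 %) support the narrower statement that brushing adds little to an indicated bronchoscopy.

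This rests on three assumptions. The study procedure means what the Enrollment section says. The zero count in 115 is a best case and not a reported whole-procedure result. The SD group is taken as a proxy for test-only use, although it also includes bronchoscopies done for other research studies, in a number not given in the visible text. The conclusion is that the stated evidence and the stated claim do not match; the documents do not show that the procedure is unsafe or that events were left out.

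**What to change.** Using the data already collected and graded:

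1. Tabulate adverse and serious adverse events related to any part of the bronchoscopy, separately for SD and SOC subjects. For SOC, show brushing-attributed events alongside.
2. Base the statement on safety of LCRT-only collection on the SD group, with an exact interval, and note that this group was slightly younger and had less COPD.
3. Use the SOC group as support for the added risk of brushing only.
4. Reword the safety summary in the Discussion and the sentence in the Conclusions so that each says whether it concerns brushing or the whole bronchoscopy. Carry the same wording into the Abstract and the benefit-risk sentence.

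The work is re-tabulation and rewording, with no new data. The price is a denominator of 115 for the test-only claim and a less favourable statement than the present one.
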